### Refinements to intervention based on Pilot Stage

A series of key observations drawn from the suite of qualitative methods employed were noted during the Pilot Stage: most staff who participated in interviews and ECPs who participated in the questionnaire and/or focus group viewed UTI guidelines as only relevant to residents without dementia, despite the guidelines’ validation in LTCHs with residents with and without dementia ((37,38)). To address this challenge, two adjustments were made to the protocol: 1) the addition of an optional peer-to-peer conversation between the medical leadership of the LTCH and a physician member of the study’s expert working group and 2) the revision of educational materials to highlight validation of guidelines in LTCHs and share experience in management of residents with dementia, including those that are non-communicative. For a full accounting of revisions in response to preliminary findings, see Appendix A.

Findings from the questionnaire, focus group and observations by staff interviewees and the Local Implementation Team indicated that the educational component of the intervention was generally appreciated by the ECPs, seeing it as relevant to their role as caregiver. However, it was observed across our qualitative data that ECPs constituted a heterogenous group and scheduling was, at times, challenging. Therefore, we increased our flexibility to offer multimodal delivery of educational materials (i.e., poster, handout, in-person session, video).

Regarding the feedback letter, members of the Local Implementation Team and all interviewed staff (n=3) expressed uncertainty about the intended use and action. Some concerns regarding the peer-comparison were also raised, highlighting the challenge of inter-home comparisons. To address these challenges, the following changes to the protocol were made: 1) inclusion of an estimate of proportion of urine cultures aligned with guidelines to provide a more actionable metric, 2) shift from peer-comparison to self-comparison to emphasize continual self-improvement and 3) highlighting links to additional supports and resources.

## Conclusion

This study will rigorously evaluate the impact of a behavioural science-informed intervention to improve AMS across LTCHs. If successful, this model of care could be scalable across Canadian LTCHs, offering an inclusive approach that aims to empower clinicians, non-regulated healthcare staff, residents and their family and friends to improve health outcomes as antibiotic stewards.

## Appendices

### Appendix A: Protocol refinements

The following table summarizes changes made to the protocol following the Pilot Stage. The protocol described in the paper reflects these changes.

**Table ta:**

Change	Change made	Description
1	Addition of an optional peer-to-peer conversation between physician member of the study expert working group and medical leadership at each home at the beginning of the Transition Phase	A goal of our Transition Phase is level-setting (getting everyone on the same page) about foundational AMS knowledge and practices. To facilitate this, we meet with the implementation team at each LTCH and review current practices and alignment with guidelines. To strengthen this, the protocol now includes an optional peer-to-peer conversation between a physician member of the working group and the medical leadership at each LTCH (i.e., Medical Director, Physician Chief). The intention is for these conversations to cover the evidence supporting the guidelines and the experiences the working group member had in implementing them in their practice.
2	Explicit inclusion of clinical pharmacists and personal support workers	The protocol now calls for clinical pharmacists employed by the home and non-regulated healthcare staff (sometimes referred to as personal support workers or nursing assistants) to attend the introductory education session provided during the Transition Phase, along with nursing staff and physicians. Previously these groups were not explicitly named in our protocol, despite being likely to interact with study materials present in staff areas (e.g., a monthly feedback report at the nursing station). This change appropriately includes them as important members of the clinical team that a portion of the responsibility for AMS.
3	Increased flexibility in delivery of staff introductory education session	The duration of the introductory education session was reduced to 5−10 minutes and the protocol calls for it to be presented in-person, by webinar or via recorded video at the discretion of the LTCH. This increased flexibility is intended to allow for the adaption to the unique circumstances and procedures of staff training at each LTCH. The session is now provided to nurses, physicians, clinical pharmacists and non-regulated healthcare staff (personal support workers, nursing assistants, etc.), as per change 2.
4	Narrowing of prospective data collection	The protocol now includes collection of signs and symptoms prompting all urine culture orders during the Control, Transition and Intervention Phases. This allows an estimation of the proportion of cultures that are aligned with guidelines. A measure of alignment with guidelines will allow for a more precise measure of AMS compared to rate of urine culture alone. Alignment with guidelines will be used as an exploratory evaluation of the success of the trial (pre-post comparison) as well as a component of the feedback report. To balance the additional workload to LTCHs collecting this data, the protocol also limits the previously required monthly facility-level demographic data from all residents of the LTCH to only those who received a urine culture. The previous monthly facility-level demographics provided little additional value to the cross-sectional demographic data collected with the retrospective data. If some LTCHs are unable to provide signs and symptoms data, we will 1) report this finding, which will highlight an important knowledge gap, 2) remain adequately powered to evaluate the study using rate of urine culture order and 3) antibiotic prescription for UTI as previously planned.
5	Updates to feedback letter content	The protocol now calls for the feedback letter to provide a self-comparison of LTCH urine culture order rate over time, as well as an estimate of the proportion of urine culture orders that were aligned with guidelines. Previously, the protocol called for a peer-comparison of urine culture order rate between the LTCHs included in the Trial Stage, as well as comparison with historical data. The change avoids limitations of inter-home comparisons and allows for a focus on self-comparison in the spirit of continual improvement.
6	Increased opportunity for qualitative engagement with staff	The protocol calls for a minimum of three, but opportunity for six semi-structured interviews at each LTCH. This is a change from the previous protocol which required three interviews, with no opportunity for more. The protocol also includes a voluntary online questionnaire available to LTCH staff. This mirrors the questionnaire provided to ECPs, asking about LTCH staff’s experience with our study and suggestions for improvements. Together, these changes provide opportunity to supplement qualitative findings from a previously small number of interviews, only if there is interest and capacity at each LTCH. The online questionnaire provides a mechanism for all LTCH staff to share feedback, if they choose to do so.

Abbreviations: AMS, antimicrobial stewardship; ECP, essential care provider; LTCH, long-term care home; UTI, urinary tract infection

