Behavioural science offers a useful lens for addressing antimicrobial resistance ((22)). Behavioural science frameworks have been used to understand the drivers and barriers affecting stewardship behaviours ((23)), as foundation for AMS interventions ((24–28)). In the current work, findings from an initial literature review ((29) were synthesized with stakeholder interview results into a series of mapping exercises that narrowed from a systems, to behaviour, to cognitive map. In this way, we formalized our understanding of how prescribing decisions are influenced by the context of the individual resident, their caregivers, the clinical environment, the healthcare system and the surrounding culture. We then used a barrier prioritization exercise with a working group of experts to identify barriers for our quality improvement (QI) strategies to address. This resulted in development of a two-pronged QI strategy for reducing diagnostic testing and antibiotic treatment of UTI when not clinically indicated. The first strategy consists of targeted education for essential care providers (ECPs; someone who provides important care for a resident and who is not on the medical team, e.g., family member or friend) to address ECP expectations for testing and treatment of UTI when not warranted. The second QI strategy consists of facility-level, monthly feedback about urine culture usage and reminders of guidelines, which will be given to LTCH staff to address the barrier of perceived risk of negative outcomes when choosing non-testing/treatment. Both QI strategies do not require explicit changes to work processes of LTCH staff, an important and advantageous consideration at a time when the Canadian healthcare sector faces human resource challenges.

The effectiveness of the QI strategies will be evaluated by assessing expected reductions in urine culture orders and antibiotic prescriptions for UTI. Whenever possible, we will also examine the proportion of urine cultures aligned with guidelines before and after intervention. A mixed-methods approach will evaluate the success of the study, with qualitative data helping contextualize quantitative findings.

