## Methods

### Study overview

The study will be conducted in two stages. In the Pilot Stage, the protocol was implemented in a single LTCH for process evaluation (see **Appendix A: Protocol refinements**). The Trial Stage involves implementation in eight other LTCHs across Canada, with the main objective being an outcomes evaluation. The Trial Stage is designed as a stepped-wedge cluster randomized quality improvement study (**Table 1**) using a mixed-method approach. Quantitative data will evaluate the effectiveness of the protocol at reducing both testing and treatment for UTI, and qualitative data will contextualize the findings. Long-term care homes will be randomized to different starting times for the crossover from the control to intervention phases, with staff and residents blinded to their allocation sequence. Here, we present the final protocol, including changes informed by Pilot Stage findings. For a complete list of refinements made to the protocol following the Pilot Stage, refer to Appendix A: Protocol refinements.

**Table 1 t1:** Overview of the stepped-wedge design

LTCH	Cluster	Month 1	Month 2	Month 3	Month 4	Month 5	Month 6	Month 7	Month 8
a	1	C	C	T	I	I	I	I	I
b	1	C	C	T	I	I	I	I	I
c	2	C	C	C	T	I	I	I	I
d	2	C	C	C	T	I	I	I	I
e	2	C	C	C	T	I	I	I	I
f	3	C	C	C	C	T	I	I	I
g	4	C	C	C	C	C	T	I	I
h	4	C	C	C	C	C	T	I	I

Abbreviations: C, Control Phase (usual care is given); I, Intervention Phase (implementation of intervention); LTCH, long-term care home; T, Transition Phase (initiation of intervention)

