### Data analysis

A series of descriptive (continuous variables) and frequency analyses (categorical variables) will be conducted to get a global sense of the sample responses.

Analysis will be done at the level of the LTCH as an intention-to-treat analysis. To evaluate research question 1, rate of urine culture (per 1,000 resident days) will be calculated for the retrospective data period. To evaluate research question 2a, a generalized linear mixed-effects model will be used to assess whether or not the intervention has an effect on the rate of urine culture (per 1,000 resident days). The model will include categorical, fixed effects for phase (control/intervention) and for each month to account for secular trends, as well as a random effects for LTCH. Data from the Transition Phase will be excluded from these analyses as we do not consider these data to be clearly Control or Intervention Phase data. To evaluate research questions 2b and 2c, a similar model will be used with the outcome measures rate of antibiotic prescriptions for UTI and total antibiotic prescriptions per 1,000 resident days. Exploratory analyses will use a similar model to evaluate the potential effect of the intervention on rate of urine cultures not aligned with guidelines. Alignment with guidelines will be estimated by comparing the signs and symptoms prompting each urine culture to meet the modified Loeb minimum criteria for UTI for a catheterized or non-catheterized resident ((37,38)).

Thematic analysis will be guided by ethnographic methods and Normalization Process Theory. Taking an iterative approach that draws on Grounded Theory ((35)), open-ended codes will be applied alongside selected evaluative codes developed from a Normalization Process Theory perspective ((57,58)). Ethnographic data reduction techniques will be applied to surface focused insights to support the overarching research questions for the study ((34,36,59)).

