### Appendix B: Outcome metrics

The intervention study will be collecting data on the following key outcomes:

1. Outcomes related to urine culture orders

a. Baseline prevalence of urine cultures for diagnosis of urinary tract infections (UTIs)

b. Effect of intervention on decreasing rate of urine culture orders

c. Effect of intervention on decreasing rate of urine culture orders aligned with guidelines

2. Outcomes related to antibiotic use

a. Baseline usage of antibiotics

b. Effect of intervention on reducing incidence of antibiotic prescriptions written for suspected UTIs

c. Effect of intervention on reducing duration of written urinary antibiotic prescriptions

d. Effect of intervention on reducing incidence of total antibiotic prescriptions

e. Effect of intervention on duration of total antibiotic prescriptions

3. Outcomes related to essential care provider (ECP) education

a. Long-term care home (LTCH) staff perceptions on whether ECP education reduced pressure from ECPs to collect urine cultures for testing when not clinically indicated

b. LTCH staff perceptions on whether ECP education reduced pressure from ECPs for antibiotic treatment of UTIs when not clinically indicated

4. Outcomes related to feedback letter

a. LTCH staff perceptions on whether the feedback letter reduced their perceived risk of negative outcomes when not ordering diagnostic testing or treatment for UTIs when not clinically indicated

In addition to the above, we will also be collecting data on additional outcomes to test some exploratory research questions (e.g., result of urine culture; antibiotic dosage, duration and route of administration; catheter use; ethnicity; sex; age; chronic conditions).

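### The exploratory guideline-alignment outcome is defined in conflicting ways, and the pre-post version is confounded with calendar time

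*Protocol article*

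**What the plan says.** The protocol article describes the alignment outcome in four places.

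- **Introduction.** Where possible, "we will also examine the proportion of urine cultures aligned with guidelines before and after intervention".
- **Appendix A, change 4.** On collecting signs and symptoms: "This allows an estimation of the proportion of cultures that are aligned with guidelines". Then: "Alignment with guidelines will be used as an exploratory evaluation of the success of the trial (pre-post comparison".
- **Data analysis.** "Exploratory analyses will use a similar model to evaluate the potential effect of the intervention on rate of urine cultures not aligned with guidelines". The model it is to resemble has "categorical, fixed effects for phase (control/intervention) and for each month to account for secular trends", plus a random effect for home, and leaves out Transition months.
- **Appendix B, item 1c.** "Effect of intervention on decreasing rate of urine culture orders aligned with guidelines".

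Appendix A is current text. Its opening says: "The protocol described in the paper reflects these changes".

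**The concern.** The four places disagree on three things: the measure (a proportion of cultures or a rate per 1,000 resident days), which cultures count (aligned or not aligned), and the comparison (before against after, or phase adjusted for month). Item 1c as printed also runs against the objective in the Abstract, which is to reduce testing in residents without the minimum signs and symptoms, that is, non-aligned cultures.

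The comparison matters most. The design rests on this: "Long-term care homes will be randomized to different starting times for the crossover from the control to intervention phases". The month effects use that staggering to separate the intervention from the calendar. A plain before-after contrast gives it up, so any change in ordering practice or in symptom recording over the eight months would be credited to the intervention. The measures can also point in different directions on the same data, so the reported result would depend on which sentence the analyst followed.

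**Working it through.** **The plan's own figure.** The Sample characteristics section plans for a fall from 6.5 to 5.2 cultures per 1,000 resident days: 1 − 5.2/6.5 = 0.20, the stated 20%. No figure is given for the alignment analysis.

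**1. Calendar time in Table 1**, Transition months left out:

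| Homes | Control months | Intervention months | Mean month, Control | Mean month, Intervention |
|---|---|---|---|---|
| a, b | 1–2 | 4–8 | 1.5 | 6.0 |
| c, d, e | 1–3 | 5–8 | 2.0 | 6.5 |
| f | 1–4 | 6–8 | 2.5 | 7.0 |
| g, h | 1–5 | 7–8 | 3.0 | 7.5 |

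- Control: 4 + 9 + 4 + 10 = 27 home-months; the month numbers sum to 6 + 18 + 10 + 30 = 64; mean 64/27 = 2.37.
- Intervention: 10 + 12 + 3 + 4 = 29 home-months; sum 60 + 78 + 21 + 30 = 189; mean 189/29 = 6.52.
- Gap: 6.52 − 2.37 = 4.15 months. Within each single home it is 4.5 months, so comparing each home with itself does not remove it.
- Both conditions occur only in month 4 (f, g, h Control; a, b Intervention) and month 5 (g, h Control; a to e Intervention). That leaves 27 − 5 = 22 of 27 Control and 29 − 7 = 22 of 29 Intervention home-months without a concurrent comparator.

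**2. Bias of an unadjusted pre-post difference.** With no intervention effect and a linear drift of d points per month in the aligned proportion, bias = 4.15 × d. The documents give no drift, so d is assumed over a range. The false-positive rate is a normal approximation for two independent proportions, with 200 residents × 30.4 days per home-month at 6.5 per 1,000 (about 1,068 and 1,147 cultures), 30% or 50% aligned at the start, and clustering ignored.

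| Assumed drift, points per month | Bias, points | False-positive rate at nominal 5% |
|---|---|---|
| 0.5 | 2.1 | 16–18% |
| 1 | 4.1 | 50–54% |
| 2 | 8.3 | 98% |

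**3. How the two measures respond to the planned fall.** Let p be the aligned share at baseline. Aligned cultures are then 6.5p and non-aligned 6.5(1 − p) per 1,000 days. The baseline share is not given. Illustrations use 50% and 29.5% aligned; the latter is 100% − 70.5%, borrowed from the Introduction's upper figure on unnecessary prescriptions, which does not describe cultures.

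- *Whole fall of 1.3 in non-aligned cultures:* new proportion = 6.5p/5.2 = 1.25p (possible while p is at most 0.8). This gives 50% to 62.5%, or 29.5% to 36.9%. Non-aligned rate: 3.25 to 1.95 (−40%), or 4.58 to 3.28 (−28%).
- *Both kinds fall by 20%:* new proportion = 0.8 × 6.5p/5.2 = p, no change. The non-aligned rate falls 20%.
- *Half of the fall in each kind, p = 29.5%:* aligned 1.92 − 0.65 = 1.27, so the proportion is 1.27/5.2 = 24.4% and looks worse. Non-aligned 4.58 − 0.65 = 3.93, a 14% fall.

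The second and third cases arise because the denominator of the proportion, cultures ordered, is what the intervention sets out to change.

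**4. Power once month is adjusted for**, whole fall in non-aligned cultures, Table 1 layout. For the non-aligned rate (between-home coefficient of variation 0.3, assumed): 0.80–0.82 at 50% aligned and 0.62–0.64 at 29.5%. For the aligned proportion (between-home SD 0.10, assumed): 0.58 and 0.27. The two variance assumptions are not matched, so this is only an indication that the rate is the more sensitive measure.

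**The case against.** The strongest reply is that no pre-post test is actually specified. The Introduction sentence is a statement of intent, and the Appendix A wording is a parenthesis in a table of changes. The only analysis specification is in Data analysis, and it already models non-aligned cultures with month effects. Since the article says it reflects the Appendix A changes, that section can be read as change 4 worked out in full, with pre-post as shorthand for Control against Intervention Phase. A descriptive proportion beside a modelled rate is no contradiction, and nothing primary depends on either.

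Much of this stands. The shorthand reading is possible, the outcome is exploratory, and the plan foresees that some homes may not supply the data. But that reading settles only the comparison. It does not turn a proportion into a rate, nor aligned cultures into non-aligned ones, and item 1c remains opposite to Data analysis. This is also not detail left to an analysis plan: the article states the definitions, and they differ.

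A reader might infer that the proportion is insensitive to the intended effect. The documents do not support that. The stated objective is fewer non-aligned cultures, and if only those fall the proportion rises by a quarter in relative terms.

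A reader might also infer that a downward trend in ordering is enough to bias the pre-post proportion. It is not: an even decline in all cultures leaves the proportion unchanged. The proportion itself must drift.

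**Conclusion.** The definitions conflict in current text and need to be reduced to one. An unadjusted pre-post comparison of the aligned proportion would be confounded with calendar time; the 4.15-month gap and the two overlapping months follow directly from Table 1. The resulting bias, about 2 to 8 points, rests on an assumed drift of 0.5 to 2 points per month; with no drift in the proportion there is none. The proportion responds to a fall confined to non-aligned cultures, misses a proportional fall, and can move the wrong way if aligned cultures fall proportionally more than non-aligned ones.

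Severity is low. Appendix A speaks of the success of the trial, and it would be tempting to conclude that the trial's result hangs on this comparison, but the same sentence calls the evaluation exploratory. The primary questions on culture and prescription rates are not affected.

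**What to change.** - **Introduction and Appendix A, change 4:** replace the before-after or pre-post comparison with the analysis in Data analysis: non-aligned cultures per 1,000 resident days, in the mixed model with phase and month as fixed effects and home as a random effect, Transition months excluded.
- **Appendix B, item 1c:** change it to the rate of cultures *not* aligned with guidelines.
- **Proportion aligned:** keep it as a descriptive figure by phase and in the feedback letter, and say that it is not the basis for judging the intervention effect.

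The cost is wording only. The signs and symptoms, culture counts and resident days needed are already to be collected in the Control, Transition and Intervention Phases.
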